**Fig. 2 Fig2:**
[figure not shown]
Summary of enrolment, interventions, and assessments at each study visit (SPIRIT)

#### Protein supplementation

Protein supplementation will be provided and consumed at the beginning of every dialysis session or after the NMES. A total of 25 g of protein supplements including whey and soy proteins from Maeil Co. Ltd., Korea, i.e., renal-specific supplements (Mediwell®, protein 15 g, 400 kcal) and protein isolate powder (nutria-bridge protein powder®, protein 10 g), will be mixed together and taken.

### Outcomes

#### Primary outcomes

The primary outcomes are the hand grip and leg muscle strength of the HD patients in the different interventions, as assessed by using digital hand and leg dynamometers.

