**Fig. 1 Fig1:**
[figure not shown]
Clinical trial design

The primary endpoint was the difference in hand grip and leg muscle strength at 12 weeks among the 4 treatment groups. Secondary endpoints included the following: muscle mass; physical performance, including the 10-m walking test and timed-up-and-go test; and questionnaires about QOL, physical activity, depression, and falls.

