### Interventions

#### Neuromuscular electrical stimulation

NMES will be conducted three times a week during each dialysis session for 12 weeks. NMES will be performed as follows using a 4-channel functional electrical stimulation instrument (FES-1000/5000®, Stratec, Korea): impulse type: symmetrical biphasic, impulse width 400 μs, impulse frequency 60 Hz, and impulse on-off time 4–8 s. FES-1000 and FES-5000 are only different in batteries and provide the same electrical impulse. Participants will notify if there are any unpleasant symptoms. Impulse intensity will be individually adjusted to the maximum tolerated amperage for each stimulation session (impulse intensity range 0–100 mAp). Participants will be instructed to remain relaxed in a supine position with knees in extension during dialysis. Adhesive electrodes will be attached to a total of four areas of the bilateral lower extremities: vastus medialis: 3 cm above the upper border of the patella and 5 cm below the inguinal fold, vastus lateralis: 3 cm above the superior border of the patella and 5 cm below the inguinal crease toward the anterior superior iliac crest. NMES will be administered between 1 and 3 h after dialysis for 20 min during the first week and for an additional 2 min every week thereafter until 30 min (Fig. 2).

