#### Hand grip strength and leg muscle strength

Muscle strength will be assessed by using digital hand and leg dynamometers (T.K.K.5401 and 5710e/5715, Takei Scientific Instruments Co. Ltd., Niigata, Japan). Muscle strength will be collected at baseline and during the follow-up period at intervals of 4 weeks. Digital hand and leg dynamometers can measure from 5 to 100 kg. These dynamometers were used to evaluate muscle strength in several studies of elderly people [39–41].

A digital hand dynamometer (T.K.K. 5401) will be used to measure the hand grip strength (opposite the fistula side). Participants will measure the hand grip strength in two ways: sitting and standing. Participants will be seated, with the shoulder along the body and no rotation, 90° elbow flexion, and neutral flexion to measure sitting position hand grip strength. Participants will stand up with the shoulder along the body and with no rotation, elbow extension, and neutral flexion for standing position measurement. Participants will be encouraged to grasp strongly, three times at intervals of 1 to 2 min in each way.

A digital leg dynamometer (T.K.K. 5710e/5715) will be used to measure the leg muscle strength of the knee joint extension muscles (both sides) as directed in the manufacturer’s instructions. Participants will be seated, with 90° of knee flexion, and measurements will be repeated three times at intervals of 1 to 2 min.

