### Sample size

Sample size estimation was based on detecting a mean between-group difference in leg muscle strength at the end of the study. Based on the results from an earlier study [34], the rationale mean (pooled standard deviation (SD)) for calculating the sample size was 24.82 (we chose the left leg SD, which was larger than the right leg SD of that study, to approach conservatively). Therefore, the means (SDs) of leg muscles in the NMES and control groups were 26.1 (24.82) and −8.3 (24.82), respectively.

Assuming a two-tailed hypothesis, an alpha value of 0.0083 due to the correction for type 1 error according to multiple tests, and a desired power of 80%, 13 participants are needed per group to complete the study. To allow a 25% dropout rate, we will initially recruit at least 72 participants.

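### Hand grip and leg strength are both primary with no success rule, while the sample size, and most naturally the alpha of 0.0083, cover leg strength only

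*Protocol article*

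**What the plan says.** The Primary outcomes section states: "The primary outcomes are the hand grip and leg muscle strength of the HD patients in the different interventions". The Study design section, below Figure 1, gives the contrast: "The primary endpoint was the difference in hand grip and leg muscle strength at 12 weeks among the 4 treatment groups". The abstract says the same. None of these places ranks the two outcomes, says whether one or both must be significant, or divides alpha between them.

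The Sample size section uses one of the two: "Sample size estimation was based on detecting a mean between-group difference in leg muscle strength at the end of the study". It gives means of 26.1 and −8.3 with an SD of 24.82 for leg strength, and no effect, SD or power for grip. Its significance level is "an alpha value of 0.0083 due to the correction for type 1 error according to multiple tests"; the tests behind that correction are not listed. The Statistical methods section sets significance at p below 0.05 and mentions no correction.

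On measurement, the section on hand grip and leg strength says: "Participants will measure the hand grip strength in two ways: sitting and standing". Leg strength is taken on both sides, and each measurement is made three times. For the two walking tests the article says which attempt is analysed. For the strength measures it does not.

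**The concern.** With two unranked primary outcomes, the rule for declaring success decides what the trial's error rate and power are, and that rule is absent. The two obvious readings have different faults. If a significant result on either outcome counts, the number of chances to succeed doubles, while the correction appears to have been set for one outcome. If both are needed, the trial's chance of success depends on an outcome for which nothing was assumed. Should the choice be left until results by group are known, a positive finding on one outcome could be presented as trial success whichever outcome it came from.

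**Working it through.** **Inputs** (Sample size section unless noted): difference 26.1 − (−8.3) = 34.4; SD 24.82; standardised difference 34.4/24.82 = 1.386; two-sided alpha 0.0083; power 80%; 25% dropout; four equal groups (Study design). The correlation between grip and leg strength is not given, so a range is assumed.

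**1. The plan's own figures.** Normal approximation: n = 2 × [(2.640 + 0.842)/1.386]² = 12.6, so 13 per group. Dropout: 13/0.75 = 17.3, so 18 per group, and 4 × 18 = 72. Both stated figures reproduce, so the arithmetic is not at fault.

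**2. What 0.0083 covers.** Four groups form 4 × 3/2 = 6 pairs, and 0.05/6 = 0.00833. One outcome therefore uses the whole 5%: 6 × 0.0083 = 4.98%. Two outcomes over all pairs make 12 tests, with an upper bound of 12 × 0.0083 = 9.96%.

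**3. Family-wise error under the null.** Simulation with 4 groups of 13, six pairwise t-tests per outcome at 0.0083, 200,000 runs per setting:

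| Outcome correlation (assumed) | One outcome | Two outcomes, either suffices |
|---|---|---|
| 0 | 4.1% | 8.1% |
| 0.5 | 4.1% | 7.6% |
| 0.7 | 4.2% | 7.3% |
| 0.9 | 4.1% | 6.2% |
| 1.0 | 4.1% | 4.1% |

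**4. Other readings of the rule.**
- *Both outcomes must succeed on the same pair.* Each pair can be declared falsely with probability at most 0.0083, so the total is at most 4.98%. With no effect on either outcome, the simulated error is at most about 2%. Joint power cannot exceed the leg-strength power, and it cannot be calculated because grip has no assumed effect or SD.
- *Three comparisons with control on two outcomes.* This is also six tests, and the simulated error is about 3–5%.

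**5. Cost of correcting for 12 tests.** Alpha is 0.05/12 = 0.00417 and the leg effect is unchanged. At 13 per group the expected test statistic is 1.386 × √(13/2) = 3.534.

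| Alpha | Power, normal method | Power, t-test |
|---|---|---|
| 0.0083 | Φ(3.534 − 2.640) = 81% | 74% |
| 0.00417 | Φ(3.534 − 2.865) = 75% | 64% |

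To restore 80% by the plan's own method: n = 2 × [(2.865 + 0.842)/1.386]² = 14.3, so 15 per group; 15/0.75 = 20; 4 × 20 = 80 patients. By the t-test it is 17 per group, 23 after dropout, 92 in total.

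**The case against.** The strongest reply is that the article never says what the six tests are. They could be three comparisons with control on each of two outcomes, and then 0.0083 would hold 5%. This stands as a possibility, so a reader should not infer that 0.0083 certainly fails. It is the less natural reading: the endpoint is a difference among all four groups, and the paragraph containing 0.0083 concerns leg strength only. Requiring both outcomes would also hold the error, but no such rule is written, and it leaves the power unstated.

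Four stronger readings are tempting and are not supported:

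- *That there are four primary variables (sitting grip, standing grip, right leg, left leg), with a still larger error.* The text on positions and sides is a measurement procedure. The article names two outcomes, and reducing repeated measurements to one variable may be settled in the full protocol or analysis plan. Multiplicity grows only if each version is tested.
- *That the error is above 30%.* For two outcomes that follows from testing at 0.05 as in Statistical methods. This is a separate conflict with the Sample size section. It makes matters worse but is not the size of this point.
- *That correcting for 12 tests cuts power from 80% to 64%.* The 64% is a t-test figure, and its baseline by the same method is 74%.
- *That grip is unsuitable because stimulation goes only to the thighs ("Adhesive electrodes will be attached to a total of four areas of the bilateral lower extremities").* Two of the three active arms include protein, which has no such anatomical limit. What stands is that the assumed leg effect cannot be carried over to grip.

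It may also be said that the analysis plan would settle the matter. The choice of primary outcomes and the basis of the sample size are stated in this article, however, and as stated they do not match.

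**Conclusion.** The point holds in conditional form. Two outcomes are primary, and the sizing covers one of them; so, on the most natural reading, does the correction. If all six pairs are tested on both and either suffices, the family-wise error is about 6–8% instead of about 4%, for assumed correlations of 0.9 down to 0. If both must succeed, the error is within 5% but the trial has no stated power. Correcting for all 12 tests costs about 7 percentage points of power by the normal method, or about 9 by the t-test. These power figures take the plan's leg effect and SD as given and assume 13 completers per group. The excess in error is moderate. The main defect is that the success rule remains open while the trial is recruiting.

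**What to change.** Before outcome data are unblinded or analysed, amend as follows:

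- **Primary:** leg strength at week 12 as the sole primary endpoint, reduced to one prespecified summary variable (for example, the mean of the two legs' best attempts). State that its six pairwise comparisons are each tested at 0.0083.
- **First key secondary:** hand grip in one named position. Test a group pair on grip at 0.0083 only if the same pair is significant on leg strength. Each pair then spends at most 0.0083 over its two steps, and the total stays at 6 × 0.0083 = 4.98%.
- **Alternative, if both stay primary:** state that either suffices, apply Holm over all 12 comparisons, and restate the power. For the smallest p-value, Holm starts at 0.05/12, where leg-strength power at 13 per group is 75% (normal) or 64% (t-test). Restoring 80% at that level takes 80 or 92 patients respectively.

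Under either option, bring the significance level in Statistical methods into line for the primary comparisons.

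Cost: a dated protocol and registry amendment during recruitment. The first option needs no extra patients, but hand grip loses its primary label. The alternative keeps the label at lower stated power or a larger sample.

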#### Secondary outcomes

Secondary outcomes include the difference between treatment arms and the change throughout the study period of (1) nPCR, (2) muscle mass through bioelectrical impedance analysis, (3) physical performance assessed by gait speed through a 10-m walking test and the timed-up-and-go test (3 m), and (4) questionnaire surveys. Questionnaire surveys included the Kidney Disease Quality of Life (KDQOL) short form, International Physical Activity Questionnaire (IPAQ), Korean version of Physical Activity Scale for the Elderly (PASE), Geriatric Depression Scale, and Korean version of Falls Efficacy Scale (FES).

### Measures

#### Biochemistry

We will collect biochemical data at baseline and follow-up every 4 weeks for 12 weeks, including hemoglobin, BUN/ SCr, calcium/phosphorus, intact PTH, total CO_2_, AST/ALT, total protein/ albumin, total cholesterol, hs-CRP, 24-h urine urea nitrogen/nPCR, and Kt/V.

#### Hand grip strength and leg muscle strength

Muscle strength will be assessed by using digital hand and leg dynamometers (T.K.K.5401 and 5710e/5715, Takei Scientific Instruments Co. Ltd., Niigata, Japan). Muscle strength will be collected at baseline and during the follow-up period at intervals of 4 weeks. Digital hand and leg dynamometers can measure from 5 to 100 kg. These dynamometers were used to evaluate muscle strength in several studies of elderly people [39–41].

A digital hand dynamometer (T.K.K. 5401) will be used to measure the hand grip strength (opposite the fistula side). Participants will measure the hand grip strength in two ways: sitting and standing. Participants will be seated, with the shoulder along the body and no rotation, 90° elbow flexion, and neutral flexion to measure sitting position hand grip strength. Participants will stand up with the shoulder along the body and with no rotation, elbow extension, and neutral flexion for standing position measurement. Participants will be encouraged to grasp strongly, three times at intervals of 1 to 2 min in each way.

A digital leg dynamometer (T.K.K. 5710e/5715) will be used to measure the leg muscle strength of the knee joint extension muscles (both sides) as directed in the manufacturer’s instructions. Participants will be seated, with 90° of knee flexion, and measurements will be repeated three times at intervals of 1 to 2 min.

### Body composition

We will collect anthropometric data, including weight, height, and circumferences of the waist, upper arm, and calf. Anthropometric data will be collected after the HD. Waist circumference will be measured at the midline level between the inferior margin of the ribs and the superior border of the iliac crest. Arm circumference will be measured with 90° elbow flexion at the midline level between the greater tubercle of the humerus and the olecranon of the ulna. Calf circumference will be measured at the thickest part with knees bent at 90° in the chair.

Muscle mass will be measured by using an InBody S10 (Seoul, South Korea), an instrument based on bioelectrical impedance analysis. InBody S10 can measure intracellular fluid, extracellular fluid, and water ratio and show muscle and lean body mass by body part. We will collect data including skeletal muscle mass (SMM), SMM/body weight (%), appendicular skeletal muscle mass (ASM), ASM/body weight (%), ASM/height^2^, lower extremity skeletal mass (LESM), LESM/body weight (%), LESM/height^2^, total fat mass, and percent body fat. This instrument was used in several studies evaluating body composition in HD patients [42, 43]. Participants will have their muscle mass evaluated within 30 min after HD.

Body composition will be collected at baseline and during the follow-up period at intervals of 4 weeks.

### Performance tests

#### 10-m walking speed test

A 10-m walking course should be open at least 60 cm from both ends and is comprised of a 6-m measurement course and a 2-m acceleration and deceleration zone. Participants walk with normal walking speed after the instruction of the examiner. Participants can use walking aids such as walking sticks or canes. We will adopt a dynamic start method. Participants start walking 2 m prior to the measurement point (acceleration zone) and ended 2 m after the measurement point (deceleration zone). Participants repeat the walking speed test 2 times, and faster data will be analyzed.

#### Timed-up-and-go test

Participants will be seated close to the back and stand and walk 3 m and turn around the marked point and return to the starting point after the instruction of the examiner. Participants repeat the timed-up-and-go test 2 times, and faster data will be analyzed.

### Questionnaire survey

#### Quality of life [44]

We will use the Kidney Disease Quality Of Life (KDQOL) short form version 1.3 to evaluate health-related QOL. The KDQOL short form was developed to evaluate the QOL of CKD and dialysis patients and is a self-report format. It has been widely used and validated. It consists of 43 kidney disease-related questions, 36 physical and mental health-related questions, and 1 general health state question. Scoring algorithms given in the user manual will calculate scores ranging from 0 to 100. The scores represent the percentage of the total possible score achieved, with 100 representing the highest QOL.

#### International Physical Activity Questionnaire (IPAQ) [45]

We will use the short self-administered version of the IPAQ that covers activity in the last 7 days. It comprises 7 items that are open-ended questions surrounding individuals’ last 7-day recall of physical activity. The IPAQ evaluates the usual physical activity that people perform as part of their everyday lives. It comprises job-related physical activity, transportation physical activity, housework, house maintenance, caring for family, recreating, exercise, and sport. Vigorous physical activities refer to activities that take hard physical effort and make breathing much harder than normal. Moderate activities refer to activities that take moderate physical effort and make breath somewhat harder than normal.

#### Korean version of the Physical Activity Scale for the Elderly (PASE) [46]

The Physical Activity Scale for the Elderly (PASE) is an easily administered and scored instrument that measures the level of physical activity in individuals aged 65 years and older. It comprises self-reported occupational, household, and leisure activity items over a 1-week period. The PASE scoring algorithm was derived from physical activity measured by movement counts from an electronic physical activity monitor, activity diaries, and self-assessed activity levels in a general population of non-institutionalized older persons. PASE scores are calculated from weights and frequency values for each of 12 types of activity. The sum of the PASE scores may range from 0 to 400 or more.

#### Depression (Geriatric Depression Scale) [47]

The Geriatric Depression Scale is a self-reported measure of depression in older adults. We will use the short form of the Geriatric Depression Scale, which is comprised of 15 items. This form can be completed in approximately 5 to 7 min. Of the 15 items, 10 indicate the presence of depression when answered positively while the other 5 are indicative of depression when answered negatively.

#### Korean version of Falls Efficacy Scale (FES) [48, 49]

The Falls Efficacy Scale assesses the perception of balance and stability during activities of daily living. It assesses fear of falling in the elderly population. A 10-item questionnaire estimate confidence in their ability to perform 10 daily tasks without falling as an indicator of how one’s fear of falling impacts physical performance. Each item is rated from 1 (very confident) to 10 (not confident at all), and per item ratings are added to generate a sum. Total scores can range from 10 (best possible) to 100 (worst possible). Lower scores indicate more confidence, and higher scores indicate lack of confidence and greater fear of falling.

### Informed consent

A trained research physician or investigator will introduce the trial to the patients and inform the patients of the details of the trial, including the use of NMES, protein supplementation, and adverse reactions. At the same time, informed consent in written form will be provided for patients to read. Only when patients fully understand the process of the trial, they can choose to participate voluntarily or give up. Patients who are disabled in reading or writing should be informed through their guardians or caregivers and sign informed consent on behalf of them.

### Harms

Adverse events are defined as any unfavorable and unintended signs, symptoms, or diseases, whether or not considered related to interventions. Every adverse event will be fully recorded on the case report form, and serious adverse events will be reported to the Institutional Review Boards concerned within 24 h after the recognition.

### Ancillary and post-trial care

Any study participant who wants to change or maintain the intervention after the completion of the study can receive the corresponding treatment as they want.

### Quality control, data management, and monitoring

This study is organized by a team comprised of a principal investigator and co-investigators who take part in the design and implementation of the study. For quality control purposes, all the researchers will be trained to be well-acquainted with the study protocol and to perform tests in one unified way before the recruitment of participants. The interventions will be performed by one expert at each hospital. All data will be put onto a computer with password protection by a staff blinded to the group allocation. The original forms of data will be archived securely at the central coordinating institution. All the investigators will be responsible for data monitoring, which is performed after each subject’s participation is completed. Monitoring includes assessment of the progress of the study and verification of accuracy as well as the completeness of recorded data. After completion of the study, we will submit the original data and results to IRBs of participating institutions, and after the publication of results, we will disclose original data and results to the public. Audits will be held annually by the IRBs of participating institutions.

### Sample size

Sample size estimation was based on detecting a mean between-group difference in leg muscle strength at the end of the study. Based on the results from an earlier study [34], the rationale mean (pooled standard deviation (SD)) for calculating the sample size was 24.82 (we chose the left leg SD, which was larger than the right leg SD of that study, to approach conservatively). Therefore, the means (SDs) of leg muscles in the NMES and control groups were 26.1 (24.82) and −8.3 (24.82), respectively.

Assuming a two-tailed hypothesis, an alpha value of 0.0083 due to the correction for type 1 error according to multiple tests, and a desired power of 80%, 13 participants are needed per group to complete the study. To allow a 25% dropout rate, we will initially recruit at least 72 participants.

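### The planning means for leg strength can only be changes from baseline, while the primary endpoint is strength at 12 weeks, so the stated 80% power is not shown for that endpoint

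*Protocol article*

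**What the plan says.** The Sample size section describes its target as "detecting a mean between-group difference in leg muscle strength at the end of the study". It takes its inputs from one earlier study: "the rationale mean (pooled standard deviation (SD)) for calculating the sample size was 24.82", chosen as the larger of the two legs' SDs. It then states that "the means (SDs) of leg muscles in the NMES and control groups were 26.1 (24.82) and −8.3 (24.82), respectively". No unit is given, and the word change does not appear. With a two-sided alpha of 0.0083, the section concludes: "a desired power of 80%, 13 participants are needed per group to complete the study". A 25% dropout allowance brings the total to 72.

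The section on hand grip and leg strength measurement says: "Digital hand and leg dynamometers can measure from 5 to 100 kg".

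The text under Fig. 1 in Study design says: "The primary endpoint was the difference in hand grip and leg muscle strength at 12 weeks among the 4 treatment groups". The abstract words the endpoint in the same way, and Primary outcomes names the strength itself. None of these mentions change from baseline. Secondary outcomes, by contrast, lists change over the study period alongside differences between arms.

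Statistical methods plans two-sample t-tests or rank sum tests between groups, adds analysis of covariance, and also plans repeated-measures mixed models adjusted for baseline imbalances. It does not say which of these is primary.

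**The concern.** The section presents its inputs as something they cannot be. An instrument whose lowest reading is 5 kg cannot give a mean of −8.3, so the two means describe how strength changed, in kg or in percent. The SD of 24.82 presumably belongs to the same quantity. The primary endpoint is a level at 12 weeks.

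The SD of a change and the SD of a level are different quantities. The change SD removes the stable differences between patients, and the level SD keeps them. A power figure built on one does not automatically hold for the other. It is also the only justification given for enrolling 72 patients. The mismatch matters most if the unadjusted two-sample test on 12-week strength turns out to be the primary comparison, which the article leaves open. If the inputs are percentages, they are not on the endpoint's scale at all.

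**Working it through.** **Inputs** (all from Sample size): means 26.1 and −8.3, so difference d = 26.1 − (−8.3) = 34.4; SD 24.82; two-sided alpha 0.0083 (0.05/6, which matches the six pairwise comparisons of four arms); power 80%.

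**Reproducing the plan.** n per group = 2 × (SD/d)² × (z₁₋α/₂ + z₀.₈)² = 2 × (24.82/34.4)² × (2.640 + 0.842)² = 12.62, rounded up to 13. Dropout: 13/0.75 = 17.3, rounded up to 18; 4 × 18 = 72. Both stated figures reproduce, so the change-type inputs did set the trial size.

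**Reference point.** With these inputs and 13 per group, power is 81.4% by the normal approximation and 73.7% by the exact (noncentral) t-test. The results below use exact t, so the fair comparator is 73.7%, not 80%.

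**From change to level.** The documents give no SD for 12-week leg strength and no correlation. Assume that 24.82 is the SD of an absolute change in kg, that the variance is equal at both visits, and that r is the correlation between baseline and week 12. Then:

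- SD of the 12-week level = 24.82 / √(2(1 − r)).
- SD after baseline adjustment = level SD × √(1 − r²) = 24.82 × √((1 + r)/2), which never exceeds 24.82.
- Under randomisation, the expected group difference is 34.4 on either scale.

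| r (assumed) | level SD | power, unadjusted 12-week strength | adjusted SD | power, baseline-adjusted |
|---|---|---|---|---|
| 0.3 | 21.0 | 89% | 20.0 | 92% |
| 0.5 | 24.8 | 74% | 21.5 | 87% |
| 0.6 | 27.7 | 61% | 22.2 | 85% |
| 0.7 | 32.0 | 46% | 22.9 | 82% |
| 0.8 | 39.2 | 29% | 23.5 | 79% |

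All rows use 13 per group and alpha 0.0083. The adjusted column ignores the small cost of estimating the covariate effect.

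**Upper limit on r.** Readings confined to 5 to 100 kg cannot have an SD above 95/2 = 47.5 kg. Setting 24.82/√(2(1 − r)) = 47.5 gives r = 1 − 24.82²/(2 × 47.5²) = 0.86. Higher correlations are incompatible with these assumptions, so they are left out. An SD of 39.2 kg at r = 0.8 is already near the edge, since many readings would have to lie close to both ends of the range.

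**If the values are percent changes.** Converting them to kg needs the baseline strength distribution, which the documents do not give. No power for strength in kg can then be derived, whatever the model.

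**The case against.** The strongest reply is that the article already plans baseline-adjusted analyses, and that with those the mismatch costs nothing. Under the assumptions above, the adjusted power is 79% to 92%, always above the 73.7% that the plan's own inputs give by the same method. A second reply is that the target is not really a different one: with randomised groups, the expected difference in absolute change equals the expected difference in 12-week strength, so only the error term can differ. A third is that Statistical methods does not say whether the two-sample tests use levels or changes, and that the full protocol may give the unit.

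Most of this stands. A reader might infer that the trial is underpowered. The documents do not support that: they contain neither r nor a level SD, an unadjusted comparison loses power only above r = 0.5 and gains below it, and an adjusted analysis loses none. A reader might also infer that the inputs are percentages, but the documents do not settle this either way.

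What the reply does not remove is the labelling fault, which is more than an omitted detail: the printed text describes the inputs as end-of-study strength, and −8.3 cannot be that. Nor does the article make an adjusted analysis primary, and adjustment helps only if the inputs are absolute changes.

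**Conclusion.** The point holds as a mismatch between the planning inputs and the endpoint. The arithmetic behind 13 per group and 72 in total is sound. Its inputs are changes of unstated unit, the primary endpoint is strength at 12 weeks, and the 80% power is therefore not shown for that endpoint.

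The size of any loss is conditional. For absolute changes in kg with equal variances, an unadjusted test of 12-week strength drops from 74% at r = 0.5 to 46% at r = 0.7 and 29% at r = 0.8, but has 89% at r = 0.3. A baseline-adjusted comparison does at least as well as the planning inputs throughout. For percent changes, no power figure for strength in kg is supported. The impossibility of −8.3 as a strength follows from the documents alone; the power figures rest on the stated assumptions.

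**What to change.** 1. In Statistical methods, name the baseline-adjusted comparison of week-12 leg strength in kg as the primary analysis, in place of the unadjusted two-sample test. This can be ANCOVA, or the planned mixed model with baseline strength as a covariate. Change from baseline adjusted for baseline is equivalent. Word the primary endpoint to match.
2. In Sample size, state that 26.1, −8.3 and the SD of 24.82 are changes, and give the unit and the leg.
3. If they are percentages, redo the calculation on the kg scale and restate the power for 72 patients.

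Items 1 and 2 cost only wording, because baseline strength is already measured and the adjusted methods are already named. The downside lies in item 3: the restated power may be less favourable than 80%.
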